### Study Design, Participants, and Recruitment

#### Phase 1—Risk and Needs Assessment

##### Overview

This phase will involve formative, qualitative research using individual web-based interviews and focus group discussions with key informants (young Black men and service providers). This needs elicitation phase will identify social and structural barriers and motivators influencing youth violence and substance use prevention services among Black boys and men (aged 15-24 years) and their service providers (including but not limited to health care providers, street outreach workers, social workers, violence interrupters, community advocates, and school staff). In separate focus groups and individual interviews, we will include community barrier mapping and graphic facilitation sessions (ie, displaying ideas expressed during meetings on a whiteboard with text and imagery). Young Black men and service providers will describe (1) sociostructural targets to improve young Black men engagement with violence prevention services, (2) culturally salient needs, (3) knowledge of existing resources (eg, where, how, and why young Black men seek assistance), and (4) preference for digital behavior change interventions. In addition, we will age-stratify all interviews (15-17 years and 18-24 years) to account for differences in risk taking, peer culture, developmental age, and self-identity. The service providers and young Black men will not interact in the same sessions. Instead, separate sessions will be scheduled for service providers so that young Black men may openly communicate their experiences and account for developmental, background, and age differences without bias. Sessions will be conducted in person, via phone, or via secure video chat (Zoom; Zoom Video Communications Inc). The outline of the study design is shown in Figure 3.

**Figure 3 figure3:**
[figure not shown]
Outline of study design. ACTV: Achieving Change Through Values-Based Behavior; ADAPT-ITT: Assessment, Decision, Administration, Production, Topical, Experts, Integration, Training, and Testing; BrotherlyACT: Boosting Violence-Related Outcomes Using Technology for Empowerment, Risk Reduction, and Life Skills Preparation in Youth Based on Acceptance and Commitment Therapy.

##### Study Setting

Study sessions will occur concurrently, with Zoom, phone (phases 1 and 2), and in-person options for participation (phase 3). Only in Chicago, where the study researchers are based, will participants be able to undergo in-person procedures in pediatric EDs and community-based centers, if they prefer. We have chosen to start with young Black men in 1 major high-risk city (Chicago) to establish proof of concept before expanding to other cities with a high violence burden (Detroit, Baltimore, Camden, and Oakland) in the future.

##### Consent and Assent Process

Black boys aged 15 to 17 years will assent, and Black men aged 18 to 24 years will consent. Participants can electronically assent or consent on a Health Insurance Portability and Accountability Act–compliant e-consent platform. The informed e-consent form will include information about the study’s aim, procedures, confidentiality, and risks and benefits of participation and the safety and risk mitigation protocols. Alternatives for contacting the study team (ie, text, calls, and emails) will accommodate participant needs and account for digital divides, internet bandwidth issues, and digital health equity concerns (eg, privacy and data safety concerns). We will not collect written documentation of youth assent and consent to safeguard the participants’ confidentiality. We will waive parental consent as this study poses low risk, according to federal laws (45 Code of Federal Regulations 46), Section 116 (d) [72]. Waiving parental consent does not affect the rights and welfare of our participants. Low rates of young Black men enrollment when parental consent is mandated have impeded previous studies.

Moreover, young Black men with low risk (less substance use; little to no violent history) are oversampled when parental consent is mandated (individuals with high risk or great use of violence and substances are less likely to join owing to this reason). Waiving parental consent may reduce sampling biases and dishonest reporting by participants, as adolescent participants may fear their parents discovering their participation in the study. Ineligible participants will be redirected to the end of the survey, where they will find resources (eg, crisis helplines and suicide hotlines) to help young Black men obtain the needed services. In addition, once the e-consent form is submitted, participants can print or save a copy of the informed assent and consent form before moving on to the web-based survey. Importantly, there is no more than minimal risk involved in completing the brief web-based sociodemographic questionnaire, and the participants’ responses will remain completely anonymous (no IP addresses will be automatically logged in REDCap [Research Electronic Data Capture; Vanderbilt University]).

##### Consent Process for Service Providers

Service providers will be required to verbally consent at the beginning of each session. Service providers will be informed about the voluntary nature of this study, that all questions are optional, and that the session will be audio-recorded. As a part of the consenting process, service providers will be informed that they will not have access to any young Black men’s data, even if they come from the same organization.

##### Data Analysis for Phase 1

Focus groups and interviews will be audio-recorded and transcribed verbatim by an independent transcriptionist. Transcripts from the study sessions will be recorded (with permission after informed consent), transcribed verbatim, and analyzed by 2 research team members using qualitative description, low-abstraction, and low-inference approach to closely interpret the data [73-75]. Qualitative description is ideal for describing phenomena of the participants’ experience and language and is well suited for needs and risk assessment with susceptible populations [73-75]. After sorting, rearranging, and comparing codes, we will form categories and subcategories by pooling codes based on commonality, divergence, and logical parsimony [60,61,76]. Primary themes will be identified based on data generalizations and supplemented by participant excerpts [73,74]. Qualitative analysis software will be used to develop codes and a codebook. Approximately 10% of all transcripts will be double coded as pilot transcripts and reviewed for intercoder reliability or consistency to ensure high coder agreement (κ>0.80). In addition, *wish list* data will be analyzed according to a multilevel content analysis using an inductive six-phase process [76]: (1) coding of data sources (ie, focus group and interview transcripts), (2) reflexive note taking and bracketing, (3) cross-examination to discern similarities and variations in data, (4) observing commonalities and differences among the data, (5) identifying stable generalizations from the data, and (6) comparison of results with established literature.

##### Inclusion and Exclusion Criteria

Black boys and men invited to participate are eligible if they identify as male, irrespective of sexual orientation; identify as Black or African American; are aged between 15 and 24 years (inclusive); report having internet access; and are able to assent or consent to participation. We have received an IRB waiver of parental consent, as this study presents minimal risk. Those who are actively suicidal or homicidal, not medically stable, intoxicated during recruitment, and cognitively unable to provide informed consent; have impairments (such as emergent injuries); or are in police custody or incarcerated during the study enrollment will be excluded. Service providers will be adults (1) aged >18 years (all genders), (2) with experience in working with racial and ethnically diverse youths, (3) of any race or ethnicity, and (4) who are able to speak and read in English.

##### Recruitment Plan

Recruitment will be based on the Strategies to Recruit, Engage, and Retain Children in Behavioral Health Risk Factor Studies (REACH) model [77]. Strategies will include distributing flyers in high-traffic areas frequented by adolescents (eg, youth-serving agencies, festivals, churches, not-for-profit organizations, sports centers, reentry resource fairs, and barbershops). Our partner organizations will assist in recruitment using channels they deem appropriate for reaching the youth they serve. Partner organizations include The Urban Male Network and the Chicago Black Therapists Network (a network of 140 Black therapists). Both programs support underserved Black youth with mentoring and mental health services. We will also recruit through clinical research platforms, such as ResearchMatch (funded by the National Institutes of Health) [78] and The New Normal. We will work with 2 urban pediatric EDs: John H Stroger, Jr Hospital of Cook County (IRB approved), a level-1 trauma hospital that treats approximately 120,000 adults and children annually; and the 62-bed pediatric ED at Rush University Medical Center. Social media will support broadcast recruitment (via Instagram and Facebook advertisements). Service providers will be recruited via direct email to relevant organizations, word of mouth, and snowballing. Study materials will refer to the *Youth Health and Safety Study*.

A community champion familiar with the West and South sides of Chicago will advise and facilitate recruitment in these communities. Similarly, clinical research assistants in each ED or in-patient trauma unit will enroll participants presenting with assault-related or violence-related injuries who meet our eligibility criteria. All study staff will be trained in research compliance, motivational interviewing, trauma-informed research and data collection, and sensitivity training. After obtaining consent, young Black men will complete a survey on REDCap to assess their eligibility. Participants’ compensation will be graded, ranging from US $25 to US $40, with the amount increasing for each study session completed. Service providers will receive US $50 for each session they complete.

##### Retention Plan

Similarly, we will use the REACH model [77] to maximize participant retention. These strategies will include the following: (1) obtaining the names, phone numbers, and email addresses or SMS text messages of several (at least 3) individuals (ie, friends, parents, and siblings) as alternate safe contacts to keep in touch with participants; (2) after each study communication, the participant will be provided with study contact information; (3) gift card compensation and train or bus passes will be provided for in-person meetings; and (4) a secured database for organizing follow-up contacts. When the app is developed and ready for testing (ie, phase 3), retention plans will include offering participants access to a password-protected study website with instructions on how to safely use the app and maintaining periodic contact throughout the study to assess for safety and confirm planned or unplanned changes to contact information.

#### Phase 2—Adapt and Optimize BrotherlyACT

##### Overview

Pertinent themes from phase 1 will inform the adaptation of the ACTV curriculum into a microlearning format in BrotherlyACT. This stage will be focused on iteratively developing all 3 components of BrotherlyACT tailored to young Black men affected by violence and substance use. The microlearning modules will draw on the evidence-based ACTV intervention by adapting, modifying, or adding modules directly relevant to young Black men’s unique experiences in noninstitutionalized contexts. UCD principles and the 8-stage ADAPT-ITT framework will guide this adaptation process. The ADAPT-ITT framework is an 8-stage sequential guide to intervention adaptation, particularly in resource-poor settings [70,71]. Overall, 2 phases of stakeholder adaptations will occur at this stage. Stage 1 will focus on content and cultural adaptations and alpha testing. Then, stage 2 will comprise context adaptations and beta testing. UCD efforts will be informed and guided by our previous study using this methodology.

##### Stage 1

#### Overview

This phase of adaptation and optimization will involve *content* and *cultural* adaptations (ie, ADAPT-ITT stages 1-5; refer to Table S1 in Multimedia Appendix 1) and will conclude with alpha testing with topic experts and a multidisciplinary steering group (n=8-10; including the codeveloper of ACTV). This steering group will alpha test using semistructured cognitive interviews and several acceptability and feasibility questionnaires, including the 10-item System Usability Scale (SUS) [79]. The SUS can heuristically capture the perceived ease of use of BrotherlyACT (usability) and learnability (the ease with which users understand the intervention curriculum and layout). The SUS score is stable, with as few as 5 participants testing it. The SUS score must average at least 68 out of 100 (68 is the universal average acceptable score) [79,80]. The SUS is highly reliable (Cronbach α=.90), with scores >70 indicating *good* usability [80].

#### Content Adaptation

In sessions lasting 60 to 90 minutes, adaptation will focus on altering the noncore components of the ACTV curriculum, including language; simplifying ACTV modules while retaining its therapeutic values; and providing examples, case studies, and metaphors relevant to young Black men. Adaptation will also refine BrotherlyACT to determine which core components must be maintained or excluded (eg, therapeutic jargon). Specifically, we will systematically adapt ACTV skills-based modules into a paper-based microlearning curriculum (draft 0) that will be evaluated and refined independently.

Participants will be taught and will read each of the modules in the ACTV curriculum. Following each module, debriefing sessions will be completed to assess acceptability. Participants will then discuss and recommend (1) vital components to be retained, excluded, emphasized, or condensed to ensure that the adapted curriculum is appropriate for young Black men based on age, context, and community setting; (2) how to structure the module’s learning objective in line with Bloom Taxonomy (to improve knowledge, life skills self-efficacy, and motivation to learn); (3) the modules’ voice, tone, and pacing; (4) engaging formats for lesson practice and rehearsal (eg, true or false factoids, card sorting exercises, multichoice questions, and quizzes); and (5) module length. The paper-based curriculum will be drafted based on this feedback using Microsoft Word.

Next, adaptation plans will focus on how BrotherlyACT’s clinical goals (eg, life skills self-efficacy) will map to BrotherlyACT’s other in-app components and pragmatic features (safety planning toolkit and service-engagement chatbot). Overall, curriculum adaptations will consider logistical issues, such as intervention workflow, and what point-of-care organizational and community capacities are required for BrotherlyACT to be successfully implemented.

#### Cultural Adaptation

This step is vital, as identity, racial socialization, and culture are central themes in minority youth decision-making to seek and use prevention services and to facilitate great sustained engagement in treatment. Culturally adapted interventions must consider racial socialization messaging, beliefs, cultural values, contexts, and racial barriers that affect young Black men. We will also plan to incorporate culturally salient factors (ie, spirituality, Black masculinity, family support, fatherhood, a community, or *village mentality*) into draft 0. These factors influence help-seeking among young Black men [81]. In addition, we will incorporate relevant media (eg, videos of reformed young Black men), providing cultural and community icons as role models, and positive ethnic pride messaging (eg, messages countering the myth that Black boys are prone to violence). Cultural adaptation will necessitate modifying elements of draft 0 based on 8 cultural domains (language, contexts, symbols, metaphors, content, concepts, goals, methods, and context) through the lens of the Ecological Validity Model [82].

##### Stage 2

This phase of adaptation and optimization will include *context* adaptations, digitization, and *beta testing* of BrotherlyACT by a youth and community advisory board (YCAB).

#### Context Adaptation

The paper-based curriculum (*draft 0*) will be optimized into a digitized curriculum (ie, interactive web-accessible and app-accessible format) as part of BrotherlyACT (*draft 1*). Using UCD principles that incorporate youth needs [59-61,72,83], the YCAB (young Black men [n=8-12] and service providers [n=5-10]) will alpha test draft 1 for contextual acceptability, esthetics, understandability, relevance, and cultural salience. This wireframe version will not have color or graphics and will concentrate on content flow, functionality, and priority using sketches and layouts of interfaces with clickable components, buttons, and dropdowns. This stage of adaptation will increase BrotherlyACT’s suitability to be digitized.

Next, our technology partner (Hekademeia Research Solutions [84,85]) will build a prototype of BrotherlyACT (*draft 2*), beginning with the adapted curriculum. This version will be functional and reflective of the final intervention. The original ACTV is a standardized manual in a predetermined sequence of modules across 24 weeks, which may restrict its flexibility in digital format. Therefore, BrotherlyACT will allow for the nonsequential deployment of interactive micromodules (that can be completed in 5-7 minutes) in response to the urgency of youth violence and the immediate skills needed and to fulfill real-world needs in high-violence, high-vigilance contexts. We will reconvene confirmatory focus groups with our YCAB to inform a finalized version of BrotherlyACT (*draft 3—*a high-fidelity prototype).

#### Beta Testing

The YCAB will beta test draft 3 in 2 consecutive sessions (broken into 2 rounds to reduce the cognitive load on participants) and build on findings from iterative sessions. Each session will last 30 to 90 minutes to identify usability problems early, quickly, and economically to find areas for improvements and to recommend content and features to retain or remove (ie, with sufficient features and functionality for testing). The YCAB will click portions (eg, buttons on the interface) on study iPads or personal phones. They will observe, rate, and clarify content tone and esthetic issues using a semiscripted usability protocol, including *cognitive walk-throughs* (to identify content and phrases not understood or interpreted as intended in modules and app pages) based on scripted cognitive tasks. *Theater testing* will be used to clarify their cognitive processes as they react to questions about content (“what comes to mind when the app asks you if you want to redo a module?”), paraphrase or summarize app-related elements (eg, text), and identify technical issues (eg, glitching or slow-loading pages) [71].

#### Phase 3—Clinical Trial

##### Overview

Overall, 60 young Black men (not part of phases 1 and 2) will be recruited to a single-group, pretest-posttest study of the finalized version of BrotherlyACT. This pilot test will determine its early feasibility outcomes (the feasibility of recruitment and retention methods; feasibility of module co-design with youth by observing fidelity to and deviations from the study protocol; completion of outcome measures; and satisfaction, appropriateness, cultural relevance, feasibility, and acceptability of the intervention). We will also ascertain the implementation outcomes for a large trial (ie, adherence, sustainability, and usability).

Assessments will be taken at baseline (T0) and after the intervention (T1) at 10 weeks, with SMS text message prompts to complete modules and study sessions. Given the exploratory nature of this study and its focus on feasibility, acceptability, and implementation outcomes, phase 3 data analyses will not be designed to have a specified level of statistical power. Nonetheless, with sample size of N=60, pretest-posttest correlation of 0.60, and α^2^ (tailed)=.05, we estimate 80% power to detect a pretest-posttest change of Cohen *d*≥0.33 (a small to medium effect). We will use mean imputation on the missing items in the event of participant loss. Participants who leave the study will be compared with those who stay to identify any differences in baseline and follow-up data for descriptive purposes and to determine if data are missing at random.

##### Data Analysis for Phase 3

Pretest and posttest scores will be compared to see if participants improved, stayed the same, or deteriorated on each outcome scale. Data will be checked for missing data patterns, distributions of outliers, and variable distributions to ensure that they meet the assumptions of planned analyses. For baseline characteristics, descriptive statistics will be generated. We are limited in attributing postintervention change without a control group to the intervention. Thus, the effects observed are preliminary. All statistical analyses will be conducted using SAS. Initial data analysis will be performed to check for data quality, including allowable ranges and errors.

Generalized linear models will analyze the pretest and posttest survey measures using repeated measures analysis. As this pilot study is exploratory, we will use a *P* value <.05 to denote significant findings but not adjust for multiple tests, given the pilot nature of the study. Exploratory analyses will examine differences in rates of pretest-posttest change by baseline characteristics, including recruitment site (pediatric ED vs community). To test such moderation effects, terms for the moderator and for the moderator × time (before and after) interaction will be added to the models described previously. Significant interactions will be graphed to aid interpretation. At the end of the 10-week study period, participants will complete exit interviews via the web individually and will complete the SUS. Additional open-ended process interview questions will focus on young Black men’s perceptions of BrotherlyACT and the research experience. As part of this study, responses to exit interview questions will be recorded with permission and thematically analyzed in a qualitative phase before being combined with pretest and posttest findings.

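### Mean imputation for lost participants makes the pre-post standard errors too small; a likelihood-based analysis of the observed data should replace it

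*Protocol article*

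**What the plan says.** In the Protocol article, Methods, Phase 3—Clinical Trial, Overview:

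- Timing: "Assessments will be taken at baseline (T0) and after the intervention (T1) at 10 weeks". There is no intermediate visit.
- Missing data: "We will use mean imputation on the missing items in the event of participant loss". The article does not say which mean is meant (person, item or sample).
- Leavers are then compared with stayers "to identify any differences in baseline and follow-up data for descriptive purposes and to determine if data are missing at random". The imputation rule does not depend on what that comparison shows.
- Planning figure: "with sample size of N=60, pretest-posttest correlation of 0.60", printed alpha "α^2^ (tailed)=.05" (read as two-tailed), and "we estimate 80% power to detect a pretest-posttest change of Cohen *d*≥0.33".

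In Data Analysis for Phase 3: "Generalized linear models will analyze the pretest and posttest survey measures using repeated measures analysis". The text does not say whether this is a mixed model, generalized estimating equations (GEE) or repeated-measures ANOVA. P<.05 marks a finding as significant, with no multiplicity adjustment. Participants are also sorted into those who got better, did not change or got worse, and moderator × time terms (including recruitment site) are added to the same models.

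**The concern.** With two assessments, a participant who is lost has a baseline form and no 10-week form. The only mean that can fill the gap is one borrowed from the stayers. Every leaver then receives the same value, and the analysis treats it as a real observation. This shrinks the spread at 10 weeks, weakens the pre-post correlation and counts people who contributed no follow-up.

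At stake are the confidence intervals and P values of every pre-post outcome with missing 10-week data, including those flagged at P<.05. Two other planned analyses are exposed. A leaver whose baseline is worse than the stayers' 10-week mean is classed as improved by construction. A common fill value also pulls subgroups together at 10 weeks and can create a moderator × time effect. Retention is itself one of the feasibility questions, so some loss has to be expected.

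**Working it through.** **Inputs.** From the Phase 3 Overview: N = 60, r = 0.60, two-sided alpha 0.05, planning effect 0.33 SD. The article gives no loss rate, so loss q of 10–40% is an assumption. Scores are in SD units with equal variance at both visits, and the fill value is the mean of the observed 10-week scores.

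**1. The plan's own figure.** SD of change = √(2(1 − 0.60)) = 0.894, so 0.33/0.894 = 0.369. A paired t test with 59 df has power 80.3% (normal approximation 81.5%), and the smallest detectable effect is 0.329. The stated 80% at 0.33 reproduces if all 60 complete 10 weeks.

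**2. Standard error under completely random loss.**

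- True variance of (observed 10-week mean − baseline mean) = [1/(1 − q) + 1 − 2r]/N.
- Variance reported from the filled data = [(1 − q)(2 − 2r) + q]/N.
- The second equals the first times (1 − q), for any r. The reported SE is therefore the true SE × √(1 − q).

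At q = 0.30, the true variance is 1/42 + 1/60 − 1.2/60 = 0.0205 (SE 0.143). The reported variance is (0.7 × 0.8 + 0.3 × 1.0)/60 = 0.0143 (SE 0.120). The ratio is 0.84.

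**3. Size of the nominal 5% test.** Rejection rate with no true change ≈ 2[1 − Φ(1.96 × √(1 − q))]. It was checked by simulating 40,000 trials per setting.

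| Assumed loss | True SE | Reported SE | Ratio | Rejects (formula) | Rejects (simulated) |
|---|---|---|---|---|---|
| 10% | 0.123 | 0.117 | 0.95 | 6.3% | 6.3% |
| 20% | 0.132 | 0.118 | 0.89 | 8.0% | 7.7% |
| 30% | 0.143 | 0.120 | 0.84 | 10.1% | 9.8% |
| 40% | 0.156 | 0.121 | 0.77 | 12.9% | 12.6% |

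**4. Bias in the mean change.** Under completely random loss it is zero. If loss depends on baseline, let g be the baseline gap between leavers and stayers in SD. The stayers' baseline mean lies q × g from the overall mean, and r of that shift carries to 10 weeks. The filled mean change is therefore off by r × q × g.

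- With an assumed g = 0.5: 0.06 SD at 20% loss, 0.6 × 0.3 × 0.5 = 0.09 SD at 30%, and 0.12 SD at 40%.
- If leavers start worse, this is false improvement; if they start better, false deterioration.
- Complete cases would be off by (1 − r) × q × g = 0.4 × 0.3 × 0.5 = 0.06 SD at 30% loss, in the opposite direction. At the plan's own r, the fill does worse than no imputation.

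**5. Moderator × time.** Assume two sites a constant 0.5 SD apart, 30% random loss in each, and one common fill value. The 10-week gap becomes 0.7 × 0.5 = 0.35, a false interaction of 0.15 SD.

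**6. The alternative.** In the same simulations, a likelihood fit to all observed data (equivalent to a two-visit mixed model with unstructured covariance) had a 4.7–4.9% rejection rate under no change, about 95% coverage and bias near zero. This held for 10–40% loss, both completely random and dependent on baseline.

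**The case against.** The sentence speaks of missing items, not missing forms. The next one compares leavers and stayers on follow-up data, as if leavers might have some. An item-level rule for partly completed forms is therefore possible. That stands as an ambiguity, but the rule is tied to participant loss, and with two visits the whole-form reading is the more natural one.

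The pilot is also exploratory. It aims at feasibility and implementation, claims no designed power, calls its effects preliminary and disclaims causal attribution. Recruitment, retention and adherence do not rest on imputed scores. This lowers the priority but does not make the error bars right.

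Three stronger readings are tempting and not supported:

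- *That the method biases the pre-post change whatever happens, or always towards improvement.* Bias needs loss related to baseline or outcome, and its sign depends on who leaves. Background links service avoidance to recidivism and relapse, but it concerns prevention programs, not loss from a 10-week study. ACTV Approach reports that the parent intervention's effect held in dropouts too.
- *That the planned model already makes imputation unnecessary.* That is so only for a likelihood-based model. GEE in general needs completely random loss, and classical repeated-measures ANOVA drops incomplete cases. The article names none of these.
- *That the pre-post estimates will size the next trial.* Expected Findings says only that findings from the development work will be useful for a definitive trial.

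**Conclusion.** The point holds on the natural reading of the sentence. At any non-zero loss, the stated rule gives standard errors that are too small. The shortfall is √(1 − loss) under completely random loss, at any correlation, so a nominal 5% test runs at about 8% with 20% loss and 12–13% with 40%. Those loss rates are assumptions. The bias is conditional: zero under completely random loss, and r × loss × gap if loss depends on baseline. The 0.09 SD example, over a quarter of the 0.33 SD planning effect, rests on an assumed 30% loss and 0.5 SD gap. This is a should-fix: a stated method that gives wrong uncertainty, in a pilot whose main aims do not depend on it.

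**What to change.** 1. Delete the mean-imputation sentence from the Phase 3 Overview.
2. In Data Analysis for Phase 3, state that the repeated-measures model is a likelihood-based mixed model (a generalized linear mixed model for non-normal outcomes), fitted to all participants with baseline data, with absent 10-week forms left unimputed. This is valid if data are missing at random given what the model includes.
3. If the sentence was meant only for isolated missing items within a returned form, say so, name the mean used and limit the rule to that case.

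A sensitivity analysis in which leavers did worse than stayers is optional.

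The cost is a sentence or two and a few lines of SAS. Reported standard errors rise, in simulation from about 0.118 to 0.127 at 20% loss and from 0.119 to 0.135 at 30%. Valid power at 0.33 SD under completely random loss is then about 76%, 72%, 66% and 60% at 10%, 20%, 30% and 40% loss. The 80% figure needs all 60 to complete 10 weeks, and imputation adds no information that would restore it.

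### The leaver–stayer comparison uses follow-up scores that leavers will not have, and it cannot determine whether data are missing at random

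*Protocol article*

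**What the plan says.** Phase 3 enrols 60 young men who "will be recruited to a single-group, pretest-posttest study of the finalized version of BrotherlyACT". The Overview fixes two measurement points: "Assessments will be taken at baseline (T0) and after the intervention (T1) at 10 weeks". The System Usability Scale and the exit interview also come at the end of the 10 weeks (Data Analysis for Phase 3), so they add no earlier outcome measure.

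On missing data the Overview says two things in succession. First: "We will use mean imputation on the missing items in the event of participant loss". Second: "Participants who leave the study will be compared with those who stay to identify any differences in baseline and follow-up data", with the stated purpose "for descriptive purposes and to determine if data are missing at random". The article describes no outcome assessment between T0 and T1 and gives no expected dropout rate.

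**The concern.** The sentence has two faults.

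- **The data.** A person who leaves before week 10 has a T0 record and perhaps some app use, but no T1 score. The follow-up half of the comparison has nothing to work on.
- **The inference.** Missing at random means that, given what was observed, dropout does not depend on the values that were not observed. Here the unobserved values are the leavers' T1 scores. A comparison of observed data can show that dropout is related to baseline, which is evidence against missing completely at random. It cannot separate missing at random from missing not at random.

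The risk is a report stating that leavers and stayers did not differ, that the data are therefore missing at random, and that the pre-post change can be read accordingly. The article says the findings will inform a definitive trial, so what the pilot may conclude about attrition matters.

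**Working it through.** **1. The plan's own figure.** Inputs from the Overview: "with sample size of N=60, pretest-posttest correlation of 0.60", two-sided α of 0.05, 80% power, Cohen d of 0.33. For a paired comparison, dz = d/√(2(1−ρ)) = 0.33/√0.8 = 0.369. The noncentrality is 0.369 × √60 = 2.86 on 59 df, which gives power of 80.3%. The stated 80% reproduces, and this point does not touch it.

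**2. Which data exist for whom.**

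| | T0 | T1 (10 weeks) |
|---|---|---|
| Stayers | yes | yes |
| Leavers before T1 | yes | no |

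Only the T0 column allows a comparison. If whole T1 scores of leavers were filled with the stayers' T1 mean and then compared, the difference would be (stayers' mean) − (stayers' mean) = 0, whatever the truth. This result is conditional: the article speaks of missing items and does not say that the comparison would use imputed values.

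**3. How sensitive the baseline comparison is.** The loss rate is an assumption; 20% and 30% of 60 are shown. For a two-sample comparison the detectable gap at 80% power is about 2.8 × √(1/n₁ + 1/n₂) SD. The last two columns use the two-sided t-test with the noncentral t distribution. The 0.5 SD gap is also an assumption.

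| Leavers v stayers | Approximation | Exact detectable gap | Power for a 0.5 SD gap |
|---|---|---|---|
| 12 v 48 (20%) | 2.8 × 0.323 = 0.90 SD | 0.92 SD | 33% |
| 18 v 42 (30%) | 2.8 × 0.282 = 0.79 SD | 0.80 SD | 42% |

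**4. Whether the test can determine missing at random.** A simulation under assumed conditions: standard normal scores, correlation 0.60, true change 0.33.

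- *Missing not at random:* about 19% loss, depending only on the part of T1 that baseline does not predict. With 1,000,000 simulated participants the leaver–stayer difference at baseline is −0.001, while the mean change among stayers is 0.446 instead of 0.33. In trials of 60, the baseline test rejects in 5.2%, its nominal rate.
- *Truly missing at random:* loss depends only on baseline (assumed logit slope −0.6 per SD). The same test rejects in 41% of trials.

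So a null result does not show missing at random, and a significant result does not refute it. The sizes depend on the assumed dropout models; the logical point does not.

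**The case against.** The case for leaving the text alone is that this is an exploratory pilot with no power target, its effects are called preliminary, causal attribution is disclaimed, and the comparison is also said to be descriptive. No later analysis is made to depend on its result. All of this stands, and it limits the consequence. It does not make the follow-up comparison possible or the inference valid. Reading the phrase loosely as missing completely at random does not rescue it either: the check could refute that, but not establish it.

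It can also be said that some leavers may have partly completed T1 forms or app-use records. That is possible, but the article does not call these follow-up data, and they would not supply full T1 scores.

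A reader might infer more than the document supports:

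- *That the check reassures whatever the truth.* It does not. The baseline half can flag selective loss, with 33–42% power for a 0.5 SD gap in the cases above.
- *That selective loss, for example through re-injury or arrest, would go undetected.* The Retention Plan provides at least three alternate contacts and, in phase 3, periodic contact that includes a safety check. Retention is itself a feasibility outcome. Recorded reasons for dropout are not promised, but there are routes to them.
- *That the check itself biases the change score.* With a 0.5 SD baseline gap and 30% loss, filling leavers with the stayers' mean would shift the estimate by 0.6 × 0.3 × 0.5 = 0.09 SD (0.06 SD at 20% loss). That shift comes from mean imputation, a separate matter, and not from this comparison.

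Finally, details of a sensitivity analysis are commonly left to an analysis plan that is not shown. Their absence is therefore not the finding; the finding is the comparison and the conclusion that the article does state.

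**Conclusion.** Wrong as written, with a modest consequence. That the follow-up comparison is unavailable for anyone who leaves before T1 follows from the article's own schedule and needs no assumption. That observed data cannot establish missing at random is a matter of definition. The baseline comparison remains useful as description, but at an assumed 20–30% loss it reliably detects only gaps of about 0.9 to 0.8 SD, so its silence says little. The documents do not support a claim that the pre-post results are invalid or that selective loss would be hidden.

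**What to change.** In Phase 3, Overview:

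1. Delete the reference to follow-up data from the leaver–stayer comparison, and delete the purpose of determining whether data are missing at random. Keep the descriptive purpose.
2. Compare leavers and stayers on T0 variables and on module use before leaving, as effect sizes with 95% confidence intervals, to describe predictors of dropout.
3. Include T0 variables related to dropout in the planned repeated-measures analysis.
4. State missing at random as an assumption, and examine it in one sensitivity table, for example with leavers assigned no change and with shifts towards worse outcomes.

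Suggested wording: *Participants who leave before T1 will be compared with those who complete it on T0 variables and on module use before leaving, with effect sizes and 95% confidence intervals. This comparison describes predictors of dropout and does not test whether data are missing at random. That is an assumption, and its influence will be shown in a sensitivity table.*

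The cost is a change of wording and a little more analysis. It calls for no new outcome assessment and leaves the sample size as it is.
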